## Abstract

**Background::**

Screening mammography has led to reduced breast cancer-specific mortality and is recommended worldwide. However, the resultant doctors’ workload of reading mammographic scans needs to be addressed. Although computer-aided detection (CAD) systems have been developed to support readers, the findings are conflicting regarding whether traditional CAD systems improve reading performance. Rapid progress in the artificial intelligence (AI) field has led to the advent of newer CAD systems using deep learning-based algorithms which have the potential to reach human performance levels. Those systems, however, have been developed using mammography images mainly from women in western countries. Because Asian women characteristically have higher-density breasts, it is uncertain whether those AI systems can apply to Japanese women. In this study, we will construct a deep learning-based CAD system trained using mammography images from a large number of Japanese women with high quality reading.

**Methods::**

We will collect digital mammography images taken for screening or diagnostic purposes at multiple institutions in Japan. A total of 15,000 images, consisting of 5000 images with breast cancer and 10,000 images with benign lesions, will be collected. At least 1000 images of normal breasts will also be collected for use as reference data. With these data, we will construct a deep learning-based AI system to detect breast cancer on mammograms. The primary endpoint will be the sensitivity and specificity of the AI system with the test image set.

**Discussion::**

When the ability of AI reading is shown to be on a par with that of human reading, images of normal breasts or benign lesions that do not have to be read by a human can be selected by AI beforehand. Our AI might work well in Asian women who have similar breast density, size, and shape to those of Japanese women.

**Trial registration::**

UMIN, trial number UMIN000039009. Registered 26 December 2019, https://www.umin.ac.jp/ctr/

## Introduction

1

Several randomized controlled trials have demonstrated reduced breast cancer-specific mortality due to mammography screening programs.^[1–3]^ The Japanese guidelines for breast cancer screening recommend mammography every 2 years for women aged 40 years and older.^[4]^ However the interpretative performance of diagnostic mammography is influenced by readers’ experience and working time engaged in breast imaging.^[5,6]^ The Japan Central Organization on Quality Assurance of Breast Cancer Screening has a program to evaluate mammography readers’ ability to maintain the quality of screening. The organization rates readers on a scale of A to D according to the sensitivity and specificity of mammography reading tests. Readers with rank A or B are considered to have above-average skills and are certified by the organization.

The breast cancer screening rate in Japan was 36.9% in 2016 (from Comprehensive Survey of Living Conditions), lower than that in other developed countries. Various efforts are being made to increase the rate. Increased numbers of women screened and the use of double reading in mammography screening programs, however, creates a high workload for readers and increases economic costs. Moreover, up to 25% of mammographically-visible cancers are still not detected at screening.^[7–10]^ Thus, alternative strategies are needed to reduce readers’ burden and detect breast cancer efficiently.

Computer-aided detection (CAD) systems have been developed to help doctors read mammographic images. However, the clinical utility of traditional CAD systems is not yet determined. While some studies have reported improved readers’ performance,^[11–14]^ others have shown increased false-positive results and unnecessary biopsies due to a low specificity.^[15–17]^

The field of artificial intelligence (AI) is rapidly evolving and novel CAD systems using deep learning convolutional neural networks have been developed. Several deep learning-based CAD systems for the analysis of mammograms have been developed, some of which have already shown very promising results.^[18–20]^ AI systems that have comparable reading ability to humans help readers improve the cancer detection rate as well as reducing the reading workload by pre-selecting suspicious lesions in mammographic images. However, the image analysis algorithms have been created and studied mainly in western countries. Because Asian women characteristically have higher-density breasts than women from other ethnic groups,^[21–23]^ it is uncertain whether AI systems created based on data from western countries can apply to Japanese women. Therefore, a deep learning-based automated diagnostic system for mammograms has to be developed with data from Japanese women.

In this study, we aim to construct a deep learning-based CAD system trained using a large number of mammograms from Japanese women. A large number of learning images with high-quality readings is crucial to create a sophisticated system. Thus, we will use the mammographic images read by readers ranked grade A according to the Japan Central Organization on Quality Assurance of Breast Cancer Screening.

This trial was approved by the institutional review board of National Cancer Center Hospital East.

## Methods

2

### Objectives

2.1

The aim of this study is to construct a deep learning-based AI system to detect breast cancer on mammograms with high specificity, and to evaluate the performance of the AI system.

### Study setting

2.2

This is a multicenter retrospective study. We will use digital mammography (DM) images taken for screening or diagnostic purposes in participating institutions.

### Endpoints

2.3

The primary endpoint is the sensitivity and specificity of the AI system to detect breast cancer with the test image set. Sensitivity is calculated as the number of images in which the AI system correctly diagnoses cancer among all images with biopsy-proven cancer. Specificity is calculated as the number of images in which the AI system correctly diagnoses normal or benign lesions among all images without cancer.

### Eligibility criteria

2.4

#### Inclusion criteria

2.4.1

DM images fulfilling all the following criteria will be collected.

1.Taken after 20102.Images meeting either one of the following criteriaVisible breast cancer or benign lesions on images.Normal breast.3.If cancer or benign lesions are visible on images, their outlines can be traced manually.4.Images from patients aged 20 or older.5.Available mediolateral oblique view with or without cranial-caudal view.6.No visible axillary lymph node metastasis from breast cancer.7.Images from patients with no previous history of chemotherapy, endocrine therapy or radiotherapy.8.Images from patients who have not received any previous surgical breast procedure including partial resection, breast reconstruction, incisional biopsy, vacuum-assisted biopsy, and mammoplasty9.Read by readers ranked A according to the Japan Central Organization on Quality Assurance of Breast Cancer Screening.10.Benign lesions, breast cancer, and normal breast on images are confirmed by the following criteria.<Benign lesions>Meeting one of the following criteriaConfirmed by histopathology.Without malignancy development over at least 2 years of follow-up.Findings clearly indicating a simple cyst by mammography and other imaging modalities.<Breast cancer>Confirmed by histopathology.<Normal breast>Meeting either one of the following criteriaIn addition to the findings of mammography, ultrasonography and MRI do not detect any lesions.Without malignancy development over at least 2 years of follow-up when no other imaging modalities except mammography are performed.

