### Construction of an AI algorithm

2.5

The machine learning community has been applying deep learning in various medical imaging fields, including mammography images. Based on this work, we have developed a convolutional neural network. The neural network includes pairs of the convolutional layer and the pooling layer with the fully convolutional layers. The classification output is calculated by the softmax function.

From mammography images, corresponding masking images of breast lesions will be created manually, indicating the area of the lesions. Mammography images will then be cropped with rectangular patches so that the lesions are included in these patches, and patches will be classified as benign or malignant. Patches in which neither benign nor malignant tumors are included will also be cropped from the mammography images.

These patches will be randomly divided into the training dataset, the validation dataset, or the test dataset. The neural network will be fine-tuned to classify whether these patches contain either a benign or a malignant tumor, or neither of them.

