### Statistical analysis

2.6

The Breast Cancer Surveillance Consortium reported readers’ interpretive performance with sensitivity and specificity of around 85% and 90% respectively.^[24]^ The sensitivity of mammography was 77% in the J-SATRT trial conducted in Japan.^[25]^ Thus, we set the target sensitivity and specificity at 80% or more with the AI system. By referring to the design of previous studies.^[26]^ 15,000 DM images will be collected in this study. They will consist of 5000 images with breast cancer and 10,000 images with benign lesions. At least 1000 images of normal breasts will also be collected for use as reference data.

We will categorize images with breast cancer according to the main findings (mass, focal asymmetric density, calcification, architectural distortion). At least 750 images will be collected in each category.

There will be a limit on the number of accumulated images with each benign lesion. Simple cyst 1500; fibroadenoma or benign phyllodes tumor 1500; intraductal (intracystic) papilloma 1500; adenoma 100; adenomyoepithelioma 100; sclerosing adenosis 1000; mastopathy 1000; breast calcifications 4000; other benign disease 300 images.

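### The primary sensitivity covers only cancers that are visible and can be outlined, but its 80% target comes from figures not stated to be so restricted

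*Protocol article*

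**What the plan says.** All places are in the Protocol article.

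- **Section 2.4.1, Inclusion criteria.** The criteria are cumulative: "DM images fulfilling all the following criteria will be collected". Criterion 2 admits an image only if it shows a visible cancer or benign lesion, or is of a normal breast. Criterion 3 adds: "If cancer or benign lesions are visible on images, their outlines can be traced manually". Criterion 10 confirms the cancer label by histopathology.
- **Section 2.5, Construction of an AI algorithm.** Masks of the lesions are drawn by hand. "Mammography images will then be cropped with rectangular patches so that the lesions are included in these patches". The patches are then divided at random into training, validation and test sets.
- **Section 2.3, Endpoints.** The primary endpoint is assessed on the test images, and its sensitivity part is defined thus: "Sensitivity is calculated as the number of images in which the AI system correctly diagnoses cancer among all images with biopsy-proven cancer".
- **Section 2.6, Statistical analysis.** Two external figures are given: "readers’ interpretive performance with sensitivity and specificity of around 85% and 90% respectively", and "The sensitivity of mammography was 77% in the J-SATRT trial conducted in Japan". The conclusion follows directly: "Thus, we set the target sensitivity and specificity at 80% or more with the AI system".
- **Section 3, Discussion.** The only limitation named is that the data come from Japanese women. The section foresees AI taking some images out of human reading once it is shown to equal human readers.

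**The concern.** A biopsy-proven cancer that cannot be seen on the mammogram, or whose margin cannot be outlined, never reaches the test set. What is estimated is the chance that the AI recognises a cancer, given that the cancer is visible and traceable. The wording of section 2.3 suggests something broader, and the target in section 2.6 comes from figures presented simply as the performance of readers and of mammography.

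If those figures count cancers that mammography does not show, the AI is set an easier task than the one behind its target. The article motivates the work by the dense breasts of Asian women and foresees using AI to decide which images no human needs to read. For that use, the miss rate over all cancers matters, and this test set cannot show it.

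**Working it through.** **1. Can an occult or untraceable cancer enter the test set?**

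- As a cancer image: no. Criterion 2 requires visibility, criterion 3 requires a traceable outline, and both must be met.
- As a normal breast: no. That label needs either no lesion on ultrasonography and MRI as well as mammography, or no malignancy over at least 2 years of follow-up. A biopsy-proven cancer does not fit.
- Through the patches: no. The lesion patches of section 2.5 are cropped from masked lesions, so a cancer without a mask gives no lesion patch.

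The exclusion of occult cancers comes from criterion 2. Criterion 3 is conditional on visibility and removes the visible cancers that cannot be outlined.

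**2. The plan's own figure.** The target is 80% or more. No formula is given. It lies between the two sensitivities cited, whose midpoint is (77 + 85)/2 = 81%. It is 3 points above 77% and 5 points below 85%.

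**3. Relation between the two sensitivities.** Let v be the share of biopsy-proven cancers that are visible and traceable. The documents do not give v; it is an assumption here.

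Se(all) = v × Se(collected) + (1 − v) × Se(excluded)

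Bias = Se(collected) − Se(all) = (1 − v) × [Se(collected) − Se(excluded)]

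The bias is upward whenever the AI does worse on the excluded cancers than on the collected ones.

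**4. Numbers for an AI that just meets 80% on collected images.**

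| v (assumed) | Se(all) if 0% of the rest is detected | Se(all) if 25% of the rest is detected |
|---|---|---|
| 1.00 | 80.0% | 80.0% |
| 0.95 | 0.80 × 0.95 = 76.0% | 76.0% + 0.25 × 0.05 = 77.25% |
| 0.90 | 0.80 × 0.90 = 72.0% | 72.0% + 0.25 × 0.10 = 74.5% |
| 0.85 | 0.80 × 0.85 = 68.0% | 68.0% + 0.25 × 0.15 = 71.75% |

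The 25% column is also an assumption. It shows how much the result depends on zero detection.

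**5. Break-even against 77%.** With none of the rest detected, 0.80 × v = 0.77 gives v = 0.77/0.80 = 0.9625. If more than 3.75% of cancers are excluded, an AI that just meets the target is below 77% over all cancers. With 25% of the rest detected, 0.80v + 0.25(1 − v) = 0.77 gives v = 0.52/0.55 = 0.945.

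The figure of 85% has no break-even, because 80% is already below it at v = 1.

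**The case against.** Several objections have force.

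- **Section 2.3 is not false.** It refers to the test image set, and within that set every biopsy-proven cancer image is counted. A reader might infer a flat contradiction with section 2.4.1. The text does not support that; the fault is that the wording suggests a wider population than the set contains.
- **The benchmark denominators are not given.** It is tempting to say that the 77% and 85% include cancers missed because they were invisible. The article does not say so. What stands is that neither figure is stated to share the AI's restriction.
- **The Introduction points partly the other way.** It says that up to 25% of cancers visible on mammography go undetected at screening, so readers may reach as little as 75% on visible cancers. On that scale 80% is not obviously lenient. But section 2.6 does not derive the target from this figure, and the figure does not address traceability.
- **Original detection is not required.** A reader might infer that only cancers a human had already detected are eligible. The Discussion lets outlines draw on pathology reports and other imaging, so a cancer missed at first reading but visible in hindsight can enter.
- **Subtle findings are guaranteed a place.** Section 2.6 asks for at least 750 images in each of four finding categories, so focal asymmetric density and architectural distortion each make up at least 750/5000 = 15%. This may offset some of the bias, though only with examples that could be outlined.
- **A much larger loss is not supported.** Setting v at 0.77 would give 0.80 × 0.77 = 61.6%. That treats a sensitivity as if it were the share of visible cancers. If readers detected none of the rest, it would mean that they miss no visible cancer, which fits badly with the Introduction.
- **Handling of two views is not stated.** That a view not showing the cancer is dropped is an inference only.

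**Conclusion.** The point stands in a limited form. As written, the plan judges a sensitivity conditional on visibility (possibly in hindsight) and traceability against a target taken from figures with no such stated restriction. This selection acts upward if, as is plausible, the AI does worse on the excluded cancers. The net bias of the whole design is not quantified.

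The size is unknown. For v between 0.95 and 0.85 and no detection outside the collected set, the overstatement at the target is 4 to 12 points (80 − 76 to 80 − 68). With v near 1 it disappears. These figures are illustrations that rest on an assumed v. Comparing them with 77% further assumes that the benchmark covers all cancers.

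The consequence is for interpretation: reaching 80% would not by itself show parity with the cited reader and mammography figures.

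**What to change.** 1. **Section 2.3:** define the endpoint as sensitivity among visible, traceable, biopsy-proven cancers in the test set, and use the same wording in the Abstract.
2. **Section 2.6:** stop deriving the target from 77% and 85%, or replace them with a reader sensitivity on the same denominator.
3. **Section 3:** name the selection as a limitation, and restrict any conclusion of equality with human reading to visible, traceable cancers.

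These changes are wording only, unless a matched reader figure has to be obtained. The price is a narrower and less favourable claim.

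**Optional and costlier:** in the test portion, also score biopsy-proven cancers regardless of visibility, labelled by histology, and report the visible, traceable cancers as a subgroup. Changing the eligibility wording alone would not achieve this. The test set of section 2.5 consists of patches cut around outlines, so cancers without a mask need whole-image scoring.

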#### Exclusion criteria

2.4.2

DM images fulfilling any of the following criteria will not be collected.

1.Tomosynthesis and synthetic 2D mammographic images2.Spot compression views3.Poor image quality4.Inappropriate images as judged by the local investigators

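### The eligibility criteria do not place the mammogram before needle sampling of the lesion, which leaves room for a label-related trace in the test images

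*Protocol article*

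**What the plan says.** Section 2.4.1 (Inclusion criteria), item 8, limits collection to images from patients "who have not received any previous surgical breast procedure including partial resection, breast reconstruction, incisional biopsy, vacuum-assisted biopsy" or mammoplasty. Core-needle biopsy and fine-needle aspiration are named neither there nor in section 2.4.2 (Exclusion criteria). The nearest safeguards in 2.4.2 are a poor-quality exclusion and "Inappropriate images as judged by the local investigators".

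Section 2.2 (Study setting) makes work-up images eligible as well as screening images: "We will use digital mammography (DM) images taken for screening or diagnostic purposes in participating institutions". Their timing relative to biopsy is not stated.

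Item 10 of section 2.4.1 sets the reference standard by class. Cancers need histopathology. Benign lesions may enter by histopathology, by follow-up ("Without malignancy development over at least 2 years of follow-up"), or as imaging-typical simple cysts. Normal breasts enter on imaging or follow-up alone.

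Under section 2.3 (Endpoints), sensitivity is the number of images in which the system "correctly diagnoses cancer among all images with biopsy-proven cancer"; specificity uses all images without cancer. Section 2.5 crops patches that contain the lesion and allocates the patches at random to training, validation and test sets. Section 2.6 sets a target of at least 80% for each measure.

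**The concern.** Criterion 8 shows that the authors saw a problem with previously sampled breasts, but the line it draws is incomplete. A site could reasonably read it as allowing a work-up mammogram taken after a core-needle diagnosis, with a marker clip, haematoma or air at the lesion.

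Such a trace comes from the diagnostic process, not from the disease. Because tissue sampling is tied to class by the reference standard, the trace can carry information about the label. It would lie inside the lesion-centred patch. It would also occur in training and test patches alike, so the internal test could not reveal that the network relies on it.

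The Discussion's intended use is preselection ahead of human reading in screening, where traces of the current work-up would be absent. At stake is whether a measured sensitivity near the 80% target reflects recognition of cancer or, in part, recognition of a prior needle.

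**Working it through.** **The plan's own figure.** 5000 cancer + 10,000 benign = 15,000, which agrees with section 2.6. The article gives no power or precision formula, so nothing further can be reproduced, and the size of this effect cannot be computed from the documents. What follows uses assumed ranges.

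**1. How strongly is sampling tied to class?** Cancer: 100% sampled at some time (item 10). Normal: none required. Benign: share not given, so the caps in section 2.6 are used.
- Sum of caps: 1500 + 1500 + 1500 + 100 + 100 + 1000 + 1000 + 4000 + 300 = 11,000.
- Entities assumed to be usually named by pathology (fibroadenoma/phyllodes, papilloma, adenoma, adenomyoepithelioma, sclerosing adenosis, mastopathy): 1500 + 1500 + 100 + 100 + 1000 + 1000 = 5200, or 5200/11,000 = 47%.
- Lower bound on that group: cysts, calcifications and other benign disease can supply at most 1500 + 4000 + 300 = 5800, so at least 10,000 − 5800 = 4200 (42%) must come from it. If fibroadenoma/phyllodes may also be unsampled, 4200 − 1500 = 2700 (27%) remain.

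**2. Would a trace be informative?** Take 47% of benign lesions as sampled and post-sampling imaging as equally common among sampled lesions of both classes. A trace is then 1/0.47 ≈ 2.1 times as frequent in cancer images as in benign ones. Among the 15,000 lesion images, the probability of cancer given a trace is 5000/(5000 + 4727) = 51%, against a base of 5000/15,000 = 33%. The association is moderate, not near-perfect.

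**3. Effect on sensitivity.** Let *s* be true sensitivity, *q* the share of cancer images taken after needle sampling, and *u* the share of those in which the trace alone produces a cancer call. Measured sensitivity = *s* + *q·u*·(1 − *s*). With *s* = 75%:

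| *q* | *u* = 25% | *u* = 50% | *u* = 100% |
|---|---|---|---|
| 0 | 75.0% | 75.0% | 75.0% |
| 10% | 75.6% | 76.3% | 77.5% |
| 30% | 76.9% | 78.8% | 82.5% |
| 50% | 78.1% | 81.3% | 87.5% |

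Reaching 80% needs *q·u* = (0.80 − *s*)/(1 − *s*): 0.05/0.25 = 0.20 from 75%, or 0.03/0.23 = 0.13 from 77%.

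**4. Effect on specificity under the same rule.** Let *qb* be the share of non-cancer images with a trace. Measured specificity = *sp*·(1 − *qb·u*). With *sp* = 80% and *u* = 50%, *qb* = 2%, 5% and 10% give 79.2%, 78.0% and 76.0%.

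**5. Both together.** With *q* = 30% among sampled lesions, *u* = 50% and 47% of non-cancer images sampled:
- sensitivity changes by 0.30 × 0.50 × 0.25 = +3.75 points;
- specificity changes by −0.80 × 0.47 × 0.30 × 0.50 = −5.6 points.

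This ignores normal images, which would dilute the loss a little. The rule also lets a trace push only towards a cancer call. A trained network could instead treat the absence of a trace as evidence against cancer, which would help specificity in unsampled lesions. The sign for specificity is therefore not determined.

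**The case against.** The strongest reply is that this is unclear wording, not a demonstrated bias.

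- **The list in criterion 8 is open.** It is introduced by *including*, and it already counts vacuum-assisted biopsy, a needle technique, as surgical. A reader might infer that core-needle images are definitely admitted; the text does not go that far. This stands, but two sites can read the rule in opposite ways.
- **Histology does not mean a visible trace.** Confirmation shows that tissue was taken at some time, perhaps after the mammogram. Nothing shows that post-sampling images will be collected, or in what share. This stands, and is why the effect may be zero.
- **Benign lesions are sampled too.** The Discussion treats histology as the general rule and follow-up as the fallback, and the caps point the same way. This limits the imbalance without removing it.
- **Sites may drop unsuitable images.** They may, but the exclusion is discretionary and does not mention biopsy change, so it need not work alike across centres.
- **The full protocol may settle timing.** Possibly. However, the article sets out ten criteria and addresses prior biopsy in one of them; the point concerns where that stated line falls.

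Two stronger readings should be resisted. One is that both sensitivity and specificity would rise; step 5 shows that specificity could fall. The other is that a small share of affected images would be enough to reach the target. Assume a detection rate that jumps from 78% to 98% when a trace is present: a 10% share adds 0.20 × 10% = 2 points and reaches 80%. That follows only from starting two points below the target; from 75%, the same 20-point jump would need 5/20 = 25%.

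**Conclusion.** The point holds as a gap in the eligibility rule that can distort the primary endpoint. Needle sampling other than vacuum-assisted biopsy is not addressed, image timing relative to sampling is not fixed, histology is compulsory only for cancers, and the patch-level random split would not expose a shortcut.

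Sensitivity may be inflated: by 0 to 12.5 points over the assumed ranges (true sensitivity 75%, *q* from 0 to 50%, *u* up to 100%), and by 3.75 points at *q* = 30% and *u* = 50%. The direction for specificity is uncertain. All of this rests on assumed shares, on the assumption that needle sampling can leave visible traces, and on a simple response rule. If every collected image predates sampling, there is no effect.

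The documents do not support a claim that performance will be overstated. They do support a change before the test set is fixed, because if sampling dates are not recorded, a sensitivity just above 80% could not be defended against this explanation.

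**What to change.** State in criterion 8 how core-needle biopsy and fine-needle aspiration are to be handled. For all classes, require test-set images to predate any needle sampling of the index lesion and to show no marker clip, by checking the image date against the pathology record. Lesions and normal breasts that were never sampled meet the timing rule automatically. Post-sampling images could then remain in the training data.

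Alternatively, record the date of first sampling of the index lesion and report the primary sensitivity and specificity in pre-sampling images only.

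The rule should concern the index lesion. Barring any past sampling of the breast would be too broad, since it would remove women with an old, unrelated aspiration.

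The cost is one added date and a check against pathology information, of which the Discussion already plans to collect the diagnosis. Some test images will be lost or must be replaced. Replacement by the same woman's earlier mammogram will not always work: that image may be held at a non-participating site, or may not show a lesion that can be outlined, as items 2 and 3 require.
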